### Lifestyle changes

A weight-loss diet (5% weight loss during the study), recommendations for increasing physical activity (aerobic with moderate intensity, at least three times per week at 30–45 min), and lifestyle changes will be presented to all patients enrolled for the study by an experienced dietician placed in the polyclinic of the NIOC Central Hospital in Tehran.

### Measurements and assessments

The grade of fatty liver is to be determined in a fasting state by medical ultrasound (also known as diagnostic sonography or ultrasonography). This is a diagnostic imaging technique which applies ultrasound in order to examine the images of internal bodily organs and structures such as the liver. Its aim is often to find the source of a disease or to exclude any pathology. One radiologist will do the ultrasound diagnostic imaging for all patients to reduce human error differences.

Serum lipid profile (TC, HDL, LDL, TG) and liver enzymes (alanine transaminase (ALT), aspartate transaminase (AST)) are to be measured by using the specific kits and Hitachi analyzer (or BT-3500) device. Serum lipid profile has now become almost a routine test. These will be done in a 12-h fasting state.

Blood glucose profiles, including FBS, FBI, HOMA-IR, and QUICKI are measured by a glucose specific kit (glucose oxidase method), electrochemiluminescence ((ECL) by the cobas e *411*® analyzer device) and the following formulae, respectively:$$ \mathrm{QUICKI}=1/\left( \log\ \left(\mathrm{fasting}\ \mathrm{insulin}\kern0.5em \mu \mathrm{U}/\mathrm{ml}\right)+ \log\ \left(\mathrm{fasting}\ \mathrm{glucose}\ \mathrm{mg}/\mathrm{dl}\right)\right) $$
$$ \mathrm{HOMA}\hbox{-} \mathrm{I}\mathrm{R}=\left(\mathrm{FBI}\ \left(\mathrm{mU}/\mathrm{l}\right)\times \mathrm{FBS}\ \left(\mathrm{mmol}/\mathrm{l}\right)\right)/22.5 $$

Glucose oxidase is widely used for the determination of free glucose level in body diagnostic fluids.

Serum inflammatory factors (IL-6, TNF-α, hs-CRP), irisin, Sirt1 and PON1 are measured by using the enzyme-linked immunosorbent assay (ELISA) method (sandwich ELISA format) and specific kits.

The ELISA is a test that uses antibodies and color change to identify a substance. The ELISA is often used as a diagnostic tool in medicine [54]. The ELISA test will be done by Elisa washer (Combiwash Human®) and bioElisa reader devices (biokit® ELx800) in this study.

Food intake and physical activity are to be assessed by using a 24-h food recall (at the beginning, after 1.5 months, and at the end) questionnaire and short-form IPAQ (at the beginning and the end), respectively.

The patients will be asked to remember all consumed food and drink during the past 24 h when completing the 24-h food recall questionnaire. This questionnaire has previously been validated in Iran [55]. The intake values will be turned to g/day, based on household food scales [56]. The dietary intakes are to be calculated by using the DFP (Dorosty Food Processor) software that contains Iranian food composition tables [55]. The intake of macronutrients and micronutrients including dietary antioxidants will thus be determined.

The purpose of the IPAQ is to provide a set of well-developed instruments that can be used internationally to obtain comparable estimates of physical activity. The short version of the questionnaire is suitable for use in national and regional surveillance systems and provides information required in research work or for evaluation purposes. Three levels (categories) of physical activity are proposed: low, moderate, and high [57]. This questionnaire has been validated in previous studies [58–60] including in Iran [61, 62].

The effect of dietary intakes, including dietary antioxidants and physical activity, will be controlled by prescribing the same diet and physical activity for all patients in both groups.

Systolic and diastolic blood pressure values will be measured with a mercury manometer at the beginning and the end of the study. Values are to be recorded in millimeters of mercury (mmHg).

Weight, height and waist circumference are determined by using a digital scale, stadiometer and nonelastic tape, respectively. They are measured thus: weight without shoes, with minimal clothing, and with a 100-g accuracy; height without shoes, standing, heels against the wall, flat and forward head, and with 0.5-cm accuracy; and waist circumference with minimal clothing, midway between the last rib and the iliac crest.

Collection of blood, specimen storage, and laboratory tests are to be conducted at the NIOC Central Hospital in Tehran.

Figure 1 presents the overall contents of enrollment, interventions, and assessments. Moreover, the Standard Protocol Items: Recommendations for Interventional Trials (SPIRIT) Checklist is provided as an Additional file 1.

**Fig. 1 Fig1:**
[figure not shown]
Contents include enrollment, interventions, and assessments

The trial conduct is to be frequently audited by an assistant through an independent process.

### Data analysis

Data entry, coding, security, and storage are also to be considered. The normality of continuous variables will be determined using a Kolmogorov-Smirnov test. Continuous and categorical baseline characteristics of the groups will be assessed using a *t* test and a chi-square test, respectively. Multivariate, two-factor, repeated measures analysis of variance will be used to assess time effects and to analyze time × treatment interaction effects on all dependent variables. All statistical measurements will be reported with 95% confidence interval (CI). A *P* value < 0.05 will be considered as statistically significant. The data will be analyzed by using SPSS software.

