### The sample size

The sample size was calculated using the “two mean comparison formula” and was related to a previous study [52] which had assessed the effects of cardamom on lipid profiles. In this study, the errors I and II are considered to be 0.05 and 0.2, respectively. The mean difference of TG between the groups was 5 mg/dl, and the standard deviation of each group was 8 mg/dl. The sample size was determined to be 40 subjects in each group. In total, 80 patients were invited and randomly divided into two groups as follows:Forty overweight or obese patients with NAFLD will be given lifestyle change recommendations (weight-loss diet (5%) during the study and increasing physical activity) and a green cardamom supplement for 3 monthsForty overweight or obese patients with NAFLD will be given lifestyle change recommendations (weight loss diet (5%) during the study and increasing physical activity) and a placebo supplement for 3 months

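### The normality test has no stated consequence and one repeated-measures ANOVA serves every outcome; if some markers are right-skewed with proportional effects, power could be lower than the same data allow

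*Protocol article*

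**What the plan says.** Three statements in the Data analysis section of the protocol article matter here.

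- On distribution: "The normality of continuous variables will be determined using a Kolmogorov-Smirnov test". Nothing follows from the result: no transformation, no alternative test, no other model.
- On the outcomes: a two-factor repeated-measures ANOVA is to assess time effects and "analyze time × treatment interaction effects on all dependent variables".
- On baseline: "Continuous and categorical baseline characteristics of the groups will be assessed using a *t* test and a chi-square test, respectively", again with no alternative for skewed variables.

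The Objectives section frames every comparison as one of means, between and within groups. Under Measurements and assessments, "Serum inflammatory factors (IL-6, TNF-α, hs-CRP), irisin, Sirt1 and PON1 are measured" by ELISA. HOMA-IR is defined there as a product of insulin and glucose, and QUICKI as the reciprocal of the sum of their logs. Under Study subjects, blood is taken only at the beginning and at the end. ANCOVA appears in the list of abbreviations but nowhere in the analysis text.

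**The concern.** A normality test with no consequence either does nothing or leaves room to change the method after the data have been seen. Neither is a good basis for an analysis.

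One ANOVA of means is also a poor fit for such different variables. Concentrations of inflammatory markers and insulin, and a product index such as HOMA-IR, cannot be negative and may well be right-skewed, with treatment acting as a percentage change. On the original scale, a few high values would then inflate the SD and dominate the mean change. With only two blood samples, the time-by-treatment term is simply a comparison of mean change scores, which uses the baseline value less efficiently than adjusting for it.

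At stake is efficiency for the inflammatory objective and for the insulin markers within the first objective. The trial was planned for 80% power on TG alone, so there is no evident reserve for the other markers.

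**Working it through.** **1. The plan's own figure.** The inputs come from the sample size section: a type I error of 0.05, a type II error of 0.2 and, for the effect, "The mean difference of TG between the groups was 5 mg/dl, and the standard deviation of each group was 8 mg/dl". The section arrives at 40 per arm.

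n per arm = 2 × [SD × (z for two-sided 0.05 + z for 80% power) / difference]² = 2 × [8 × (1.960 + 0.842) / 5]² = 40.2.

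This agrees with the stated 40, and power at 40 per arm is 79.8%. The sample size is not in dispute. It sets n = 40 per arm for what follows.

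**2. What the planned test reduces to.** With two time points, the time-by-treatment F test equals a two-sample t test on the change (end minus baseline). "Raw change" in the table below is therefore the planned analysis, if values are left untransformed.

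**3. Power under assumed skewness.** None of these assumptions is in the article: log-normal values, the same log-SD at both visits, log-scale correlation 0.6 between visits, end-of-study ratio 0.7 (a 30% reduction), no dropout. Simulated power at two-sided 0.05, 40 per arm:

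| Log-SD | Raw change | Raw ANCOVA | Log change | Log ANCOVA |
|---|---|---|---|---|
| 0.5 | 0.82 | 0.95 | 0.94 | 0.97 |
| 0.8 | 0.36 | 0.52 | 0.60 | 0.69 |
| 1.0 | 0.21 | 0.31 | 0.42 | 0.49 |

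**4. Separating scale from baseline adjustment.**

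- Scale first (raw change to log change): 94 − 82 = 12, 60 − 36 = 24 and 42 − 21 = 21 points. Baseline adjustment then adds 97 − 94 = 3, 69 − 60 = 9 and 49 − 42 = 7.
- Baseline adjustment first (raw change to raw ANCOVA): 95 − 82 = 13, 52 − 36 = 16 and 31 − 21 = 10 points. Scale then adds 97 − 95 = 2, 69 − 52 = 17 and 49 − 31 = 18.

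The split depends on the order. At log-SD 0.5 either change alone recovers most of the gap. At 0.8 and above, scale is the larger part in both orders.

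**5. Sensitivity.** In a second set of simulations the proportional effect was sized for about 79% power with log change scores, with correlation 0.5 or 0.7. Raw-change power was:

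| Log-SD | Raw-change power |
|---|---|
| 0.3 | 0.72–0.73 |
| 0.4 | 0.68 |
| 0.5 | 0.64–0.65 |
| 0.6 | 0.59 |
| 0.8 | 0.49 |
| 1.0 | 0.40 |
| 1.2 | 0.31 |

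If the effect is instead a constant shift sized for 80% power on the original scale, raw-change power stays at 0.79–0.82. Raw-scale type I error was 0.034–0.052.

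**6. A check from the article's own formulae.** Apart from the glucose unit, HOMA-IR is the insulin × glucose product divided by a constant, and QUICKI is the reciprocal of the log of that product. They cannot both be normal. If QUICKI were normal with mean 0.33 and SD 0.02–0.03 (assumed values), HOMA-IR would have a log-SD of about 0.43–0.66. For this pair, then, the choice of scale matters.

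**7. The normality test itself.** On log-normal samples of 40, the uncorrected Kolmogorov-Smirnov test rejects about 6% of the time at log-SD 0.5 and 37–40% at 0.8. With the Lilliefors correction the figures are 58% and 91–92%. The article does not say which version will be used.

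**The case against.** The article names a model and is silent on scale. A repeated-measures ANOVA can be run on logged values, and a condensed article may leave transformations to a full protocol or SAP that is not shown. This stands in part. Untransformed values are an inference from the objectives' comparison of means, and a reader should not conclude that the plan rules out transformation. What remains is what the article does fix: a normality test with no role, and one model without baseline adjustment for "interaction effects on all dependent variables".

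It can also be said that the size of the loss is not derivable from the documents. That is right. Skewness, the log-SDs, the correlation and the proportional effect are all assumed. With additive effects nothing is lost by staying on the original scale, and at log-SD 0.3–0.4 the loss is about 6–11 points.

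Several stronger readings are tempting but unsupported:

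- That TG is affected too. The planning difference of 5 mg/dl and SD of 8 mg/dl come without a mean and show no skewness.
- That two of the three objective groups are compromised. The first objective lists eight variables, of which only FBI and HOMA-IR are of the type at issue. Only the inflammatory objective consists entirely of candidate markers.
- That the Kolmogorov-Smirnov test is weak at this sample size. That depends on the version run.
- That the whole power gap is due to scale. Part of it comes from baseline adjustment.

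**Conclusion.** The point holds as one of efficiency and interpretability. The normality test has no stated consequence, and a single change-type ANOVA is named for every outcome, most naturally on untransformed values and without baseline adjustment.

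Under the assumptions stated above (30% proportional reduction, log correlation 0.6), power could be about 15, 33 and 28 points below what the same 80 patients would give with log-scale ANCOVA, at log-SDs of 0.5, 0.8 and 1.0. The gap is smaller for mildly skewed markers. It is wrong to state as fact that these markers lose much of their power, or to treat them as a single block.

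A reader might also infer that the planned test is invalid. The simulations do not show that: false-positive error stays near or below 5%. The change is worth making because it costs little and uses data already being collected.

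**What to change.** Before unblinding, amend the Data analysis section as follows.

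- Drop the Kolmogorov-Smirnov test as a basis for choosing the method.
- Analyse each outcome by ANCOVA of the end value, adjusted for its baseline value.
- For hs-CRP, IL-6, TNF-α, FBI and HOMA-IR, log-transform both visits and report the ratio of geometric means with its 95% CI.
- Analyse the other markers on the original scale, with residual checks. Keep TG on the original scale so that it matches its planning difference in mg/dl, and add a log-scale analysis as a sensitivity check.

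The cost is a few sentences, with no new data and no change in sample size. The downside is that results for the logged markers are ratios rather than mean differences, so the objectives that speak of means need matching wording.

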## Randomization and intervention

Patients are divided into two equal groups using block randomization. Stratified randomization will be used to control age and gender distribution. In this study, the ratio of green cardamom and placebo supplementation groups is 1:1. The block randomization is performed by an assistant and the intervention allocation is blinded for both the investigator and subjects. The participants are randomly placed into two groups receiving whole green cardamom powder or toast powder supplements. Cardamom and placebo capsules are prepared by the Traditional Medicine Research Center (TMRC), Iran University of Medical Sciences. Each capsule contains 0.5 g of whole green cardamom or toast powder. Placebo and cardamom capsules are similar in shape, size, and color. At the beginning of the study, all placebo capsules are to be placed near the cardamom capsules so that the patients are able to smell them. Even though some cardamom volatile oils may be absorbed by the placebo capsules, this amount is considered negligible compared to the amounts that affect health indicators. The type of supplements is blinded as A and B packages for investigators and patients.

According to previous trials, the dose of whole green cardamom powder was determined to be 3 g per day [46, 52, 53]; two capsules were consumed with each meal.

The voucher number of green cardamom is *Elettaria cardamomum* (L.) Maton, Family: Zingiberaceae, PMP-669. An essential oil percentage and the total content of phenolic and flavonoid compounds of green cardamom will be assessed using high-performance liquid chromatography (HPLC) and gas chromatography mass spectrometry (GC-MS) in the institute of medicinal plants, Shahid Beheshti University of Medical Sciences, Tehran, Iran. Some polyphenolic compounds of green cardamom, whose effects have been mentioned in other articles (caffeic acid, gallic acid, quercetin and luteolin), will also be determined by using HPLC.

Supplements are to be distributed among patients once a month and their potential complications and consumption processes registered (number of consumed capsules and the returned packages). In addition, the consumption process is to be checked once a week, by telephone.

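### For outcomes measured twice, the planned time × treatment test is a change-score t test: valid, but less precise than baseline-adjusted ANCOVA, and without the age and gender strata

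*Protocol article*

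**What the plan says.** The Data analysis section of the protocol article names one model for all dependent variables: "Multivariate, two-factor, repeated measures analysis of variance will be used to assess time effects and to analyze time × treatment interaction effects". Its two factors are time and treatment. It has no baseline covariate and no term for age or gender.

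The Abstract and the Study subjects section place the blood draws, anthropometrics and blood pressure at the beginning and the end only. The 24-hour food recall is the exception, with a third assessment at 1.5 months.

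Under Randomization and intervention: "Stratified randomization will be used to control age and gender distribution", and "the ratio of green cardamom and placebo supplementation groups is 1:1".

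Under The sample size: "The sample size was calculated using the “two mean comparison formula"; "the errors I and II are considered to be 0.05 and 0.2, respectively"; "The mean difference of TG between the groups was 5 mg/dl"; "the standard deviation of each group was 8 mg/dl"; "The sample size was determined to be 40 subjects in each group". The section does not say whether that SD belongs to the end value or to the change from baseline, and it gives no baseline-to-end correlation.

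The Objectives call for comparisons both between the two groups and within each group. ANCOVA is in the abbreviation list but not in the analysis text.

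**The concern.** With two time points, the interaction test uses the baseline value only by subtracting it. Subtraction fixes the baseline coefficient at 1, whereas ANCOVA estimates it. When the correlation is moderate, subtraction adds noise, and in a trial of 80 patients this costs power on every biomarker measured twice.

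Two further consequences follow:

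- **Chance baseline imbalance.** With equal variances, the change regresses on baseline with slope rho − 1. A group that happens to start higher will therefore tend to show a larger fall. This averages to zero over randomisations, but it moves the estimate in the trial actually run.
- **Strata.** Randomisation balances age and gender, but the model does not use that balance. Where these factors predict the change, the reported standard error is larger than the true one.

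**Working it through.** **Inputs.** From The sample size: difference 5 mg/dl, SD 8 mg/dl, alpha 0.05, power 0.80, 40 per group. From the timing of assessments: two time points. Assumed, because the article does not give them: rho (0.3, 0.5, 0.7), equal variances at the two times, and the meaning of SD 8 (both readings shown).

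**1. The plan's own figure.** n per group = 2 × [8 × (1.960 + 0.842) / 5]² = 40.19, which agrees with the stated 40 (strict rounding up gives 41). A one-sided test would need 32, so two-sided is the reading that fits. With 40 per group, power is 79.8% by the normal formula and 78.8% by the noncentral t. The noncentral t is used below.

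**2. The identity.** With two time points and two arms, the interaction F equals the squared t statistic on change scores. On a simulated data set of 40 + 40, F(1,78) = 12.938 and t² = 12.938, both with p = 0.00056.

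**3. Variances**, with S the SD of a single measurement:

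- change score: 2(1 − rho)S²
- ANCOVA: (1 − rho²)S²
- ratio ANCOVA/change: (1 + rho)/2, that is 0.65, 0.75 and 0.85 at rho 0.3, 0.5 and 0.7

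At rho 0.5, ANCOVA would need about 40 × 0.75 = 30 per arm for the precision that the change score gets from 40.

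**4. Power if 8 is the end-value SD.** Change SD = 8√(2(1 − rho)); ANCOVA SD = 8√(1 − rho²).

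| rho | Change SD | ANCOVA SD | Power, change | Power, ANCOVA |
|---|---|---|---|---|
| 0.3 | 9.47 | 7.63 | 64.5% | 82.5% |
| 0.5 | 8.00 | 6.93 | 78.8% | 89.0% |
| 0.7 | 6.20 | 5.71 | 94.6% | 97.2% |

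The change SD exceeds 8 only when rho < 0.5, so only then does the stated analysis fall short of the planned power.

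**5. Power if 8 is the SD of the change.** The stated analysis has 78.8% at every rho. ANCOVA SD = 8√((1 + rho)/2).

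| rho | ANCOVA SD | Power, change | Power, ANCOVA |
|---|---|---|---|
| 0.3 | 6.45 | 78.8% | 92.8% |
| 0.5 | 6.93 | 78.8% | 89.0% |
| 0.7 | 7.38 | 78.8% | 84.9% |

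**6. Finite sample.** Estimating the baseline slope multiplies the ANCOVA variance by about 1 + 1/76 with 80 patients. This takes off about half a percentage point of power or less (for example 82.5% becomes 82.0% at rho 0.3). The ratio passes 1 only when rho > 2/(1 + 1/76) − 1 = 0.974. In simulation at rho 0.99 it was 1.009.

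**7. Imbalance, as an example.** With S = 8, the standard error of the baseline difference is 8√(2/40) = 1.79 mg/dl. At rho 0.5, an imbalance of that size shifts the change-score estimate by 0.5 × 1.79 = 0.89 mg/dl, against a planned difference of 5.

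**8. Strata.** If age and gender explain a share R² of the variance of the change (assumed 5%, 10%, 20%), the true size of a nominal 5% test that ignores them is 2[1 − Φ(1.96/√(1 − R²))] = 4.4%, 3.9%, 2.8%. The test is conservative, not inflated. The power figures in steps 4 and 5 include no contribution from the strata.

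**The case against.** The strongest reply is that nothing here is an error. The change-score test is valid and unbiased under randomisation, and covariates are often left to a fuller document. The first half stands: this is a point about efficiency. The second half does not remove the point, because the article does not leave the model open. It names one, with its factors, for all dependent variables.

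Several stronger readings are tempting and should be resisted:

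- **That the trial is underpowered by its own figures.** This needs 8 mg/dl to be the end-value SD and rho below 0.5. If 8 is the SD of the change, the stated analysis has the planned power.
- **That ANCOVA is what the sample size was calculated for.** The formula has no correlation term. On the end-value reading it describes an unadjusted end-value comparison, which coincides with ANCOVA only at rho = 0. On the change reading it describes the stated analysis.
- **That ANCOVA can never be less precise.** That is a large-sample result. With 80 patients it can lose about 1% in variance at correlations above about 0.97, which has little practical weight.
- **That leaving out age and gender widens standard errors whenever they predict the outcome.** A constant effect on level cancels in the change. Only their relation to the change matters.
- **That the repeated-measures model should be dropped altogether.** Dietary intake has three time points, and the Objectives include within-group comparisons, which the time effects address.
- **That the abbreviation list shows ANCOVA was intended.** A bare list entry shows nothing either way.

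**Conclusion.** The concern holds as a loss of precision. For continuous outcomes measured at the beginning and the end, the stated test is the change-score t test, and ANCOVA is more precise at any realistic correlation. On the triglyceride assumptions, the gain at rho 0.3, 0.5 and 0.7 is 18.0, 10.2 and 2.6 percentage points of power if 8 is the end-value SD, and 14.0, 10.2 and 6.1 points if it is the SD of the change. The direction does not depend on which SD was meant; whether the stated analysis misses its planned power does. The sizes rest on assumed correlations and on equal variances at the two times. Omitting the strata makes inference conservative to the extent that age and gender predict the change, and the article gives no figure for that. The change should be made, but the planned analysis would not give a wrong answer without it.

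**What to change.** In Data analysis:

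- For each continuous outcome measured twice, make the main between-group comparison an ANCOVA of the month-3 value on arm, baseline value of that outcome, age and sex. Report the adjusted difference with its 95% CI.
- Keep the repeated-measures model for the within-group time effects and for the dietary data at three time points.

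In The sample size, state whether 8 mg/dl is the SD of the end value or of the change.

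The cost is a few sentences. Baseline values are already collected, age and gender must be known in order to stratify, and SPSS fits the model. The Trial status section reports that recruitment was still under way at submission. The change should be fixed before unblinding.

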### Objectives

× Compare the mean serum lipid (triglycerides (TG), total cholesterol (TC), low-density lipoprotein (LDL), high-density lipoprotein (HDL)) and glucose indices (fasting blood sugar (FBS), fasting blood insulin (FBI), homeostasis model assessment-insulin resistance (HOMA-IR), Quantitative Insulin Sensitivity Check Index (QUICKI)) between the two groups and within each group, before and after intervention× Compare the mean serum inflammatory factors (TNF-α, interleukin-6 (IL-6), highly sensitive C-reactive protein (hs-CRP)) between the two groups and within each group, before and after intervention× Compare the mean of serum PON1, sirt1, and irisin between the two groups and within each group, before and after intervention

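### The article names no primary outcome although the sample size rests on triglycerides; 14 equally ranked outcomes are each judged at P < 0.05, with no hierarchy, adjustment or joint-test gate stated

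*Protocol article*

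**What the plan says.** The Objectives section of the protocol article contains three objectives of equal standing. They cover four lipids (TG, TC, LDL, HDL), four glucose indices (FBS, FBI, HOMA-IR, QUICKI), three inflammatory factors (TNF-α, IL-6, hs-CRP) and three further markers (PON1, Sirt1, irisin). That makes 4 + 4 + 3 + 3 = 14 outcomes. Each is to be compared both between and within arms; the second objective, for example, reads "Compare the mean serum inflammatory factors (TNF-α, interleukin-6 (IL-6), highly sensitive C-reactive protein (hs-CRP)) between the two groups and within each group".

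The sample size section uses one of the 14: "The mean difference of TG between the groups was 5 mg/dl", and "the standard deviation of each group was 8 mg/dl". It sets the error rates ("the errors I and II are considered to be 0.05 and 0.2, respectively") and concludes: "The sample size was determined to be 40 subjects in each group". It does not call TG primary.

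The Data analysis section plans a repeated measures analysis of variance, described as multivariate, for time effects and time × treatment "interaction effects on all dependent variables". The only decision rule is that a P "value < 0.05 will be considered as statistically significant". The same section promises 95% confidence intervals.

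The Abstract and Background give particular weight to irisin, PON1 and Sirt1. The Background hypothesis concerns improvement of NAFLD itself, yet neither liver enzymes nor fatty-liver grade appears in the Objectives.

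**The concern.** The article points in several directions at once. The sample size points to TG, the stated aim to irisin, PON1 and Sirt1, the hypothesis to NAFLD, and the analysis to everything equally. The planned 5% error and 80% power describe one test on TG, but nothing makes that test the basis of the trial's conclusion. Under the rule as written, a significant result on any of the 14 markers could be presented as the finding, whatever TG shows.

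The within-group comparisons offer further routes to a significant result. Both arms receive a 5% weight-loss diet and advice to exercise more, so a marker may change within the cardamom arm even if the capsule is inert.

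**Working it through.** **1. The plan's own figure.** Inputs from the sample size section: difference 5 mg/dl, SD 8 mg/dl, type I error 0.05, type II error 0.2. Sidedness is not stated.

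n per arm = 2 × [SD × (z₀.₉₇₅ + z₀.₈₀) / difference]² = 2 × [8 × (1.960 + 0.842) / 5]² = 40.19

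Rounded up, this is 41, against 40 stated. A one-sided test would give 32, so two-sided 0.05 is the reading that fits. Power at 40 per arm: 5 / (8 × √(2/40)) = 2.795, and Φ(2.795 − 1.960) = 0.798 (78.8% with the t distribution). The stated size is reproduced within rounding, for one test on TG.

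**2. Upper end: 14 independent outcomes, no true effect on any.**
- At least one P < 0.05 in either direction: 1 − 0.95¹⁴ = 0.512.
- At least one that favours cardamom: 1 − 0.975¹⁴ = 0.298. For a single test this figure is 0.025.

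**3. Allowing for correlation.** The documents give no correlations, so a range is assumed. With two time points, the time × treatment test is equivalent to a two-sample t test on change. This was simulated at 40 per arm with a common correlation r among the 14 outcomes (8,000 runs per row), each scored so that positive means benefit.

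| r | Either direction | Favouring cardamom |
|---|---|---|
| 0 (formula) | 0.51 | 0.30 |
| 0.2 | 0.47 | 0.24 |
| 0.3 | 0.45 | 0.23 |
| 0.5 | 0.34 | 0.18 |
| 0.7 | 0.26 | 0.12 |

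Numerical integration under a normal model agrees to within simulation error (for example 0.44 at r = 0.3 and 0.25 at r = 0.7, either direction).

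A block pattern was also simulated (20,000 runs per setting). HOMA-IR and QUICKI were almost determined by insulin, the TC–LDL correlation was 0.85, and other correlations were 0.2 to 0.4 within groups of markers and 0 to 0.2 between them. It gave 0.42 to 0.45 in either direction and 0.22 to 0.25 in favour of cardamom.

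**4. HOMA-IR and QUICKI.** By the formulae under Measurements and assessments, HOMA-IR is insulin × glucose divided by a constant, and QUICKI is the reciprocal of log insulin + log glucose, that is, of log(insulin × glucose). Apart from glucose units, both depend only on the same product, so one chance result can appear under two names.

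**5. Comparing remedies.**
- TG as single primary outcome: type I error 0.05, power 79.8% at 40 per arm, N unchanged.
- All 14 kept co-equal with Bonferroni: the threshold is 0.05/14 = 0.00357 (z = 2.914). Power for the TG difference is Φ(2.795 − 2.914) = 0.45. For 80% power, n = 2 × [8 × (2.914 + 0.842) / 5]² = 72.2, so 73 per arm.

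**The case against.** Several points on the other side have force.

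- **The 51% figure.** A reader might infer that an inert capsule has a one-in-two chance of a positive trial. The documents do not support that. The figure needs 14 independent outcomes, and the article's own formulae rule out independence for HOMA-IR and QUICKI. It also counts results that go against cardamom, which no one would report as benefit.
- **More outcomes.** The article also measures ALT, AST, weight, waist, systolic and diastolic pressure and fatty-liver grade, which would make 21. These are not in the Objectives, and the grade is ordinal, so adding them to the same family is a reader's choice. The estimate here stays with the 14.
- **Overlap.** The shared content of HOMA-IR and QUICKI lowers the family-wise rate. It matters for reporting, not as added inflation.
- **The word multivariate.** If a joint test had to be passed first, the error rate with no effect on any outcome would be 0.05. The article mentions no such requirement, so this is an ambiguity and not an answer.
- **What is not shown.** The registry record, Fig. 1 and the SPIRIT checklist are not at hand, and a primary outcome may be named there. The claim is therefore limited to this article. Multiplicity methods for secondary outcomes may properly be left to an analysis plan.

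The central point stands. The article sets out its objectives, sample size and significance rule, and these three do not identify the outcome on which the trial will be judged.

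**Conclusion.** The concern holds in limited form. This article names no primary outcome although N rests on TG, and it judges 14 equally ranked outcomes at 0.05 without a stated hierarchy, adjustment or gate. With no true effect on any of them, the chance of at least one false between-group result is about 26% to 51% in either direction and about 12% to 30% in favour of cardamom. Those ranges rest on assumed common correlations from 0.7 down to 0, on 40 per arm, and on the 14 listed outcomes only. Within-group tests add to this by an amount not estimated here.

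A reader might go further and say that the 0.05 error rate applies to nothing in the trial. That is too strong: it applies to each comparison taken singly, TG included. What is missing is the statement that ties the trial's conclusion to one of them.

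**What to change.** In a dated amendment, made before unblinding:

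1. Name TG, compared between groups at two-sided 0.05, as the single primary outcome, and base the trial's conclusion on it.
2. Label all other outcomes, including irisin, PON1 and Sirt1, and all within-group comparisons, as secondary or exploratory. Report them with the 95% confidence intervals already planned and make no confirmatory claim, or apply Holm. With the 13 remaining outcomes, Holm's first threshold is 0.05/13 = 0.0038.
3. Read HOMA-IR and QUICKI as one result on insulin sensitivity.

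If the registry record or full protocol already names a primary outcome, the article and the sample size should be reconciled with it. Should the investigators want one of irisin, PON1 or Sirt1 to lead, that outcome would need its own sample-size basis, which the article does not give.

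The cost is wording in Objectives and Data analysis; N stays at 40 per arm. The markers other than TG lose confirmatory status. Recruitment was under way when the article was submitted, so timing matters: a designation made after the data are seen would not count as prespecified.
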